## Abstract

**Background:**

The coverage of influenza vaccination among older adults in Norway is insufficient, especially in some immigrant groups. To improve public health, there is a need for an intervention that can increase influenza vaccination coverage. Further, interventions tailored to reduce potential barriers among immigrants can reduce health inequities.

**Objective:**

InfluSMS aims to determine if SMS nudging increases vaccination coverage among those aged 65 years or older (1) in Norway’s general population; (2) among immigrants born in Poland; and (3) among immigrants born in Ukraine; and evaluate the impact of SMS nudging in Norwegian versus in the official language of the native country of immigrants born in Poland or Ukraine.

**Methods:**

InfluSMS is a pragmatic randomized controlled trial conducted among people aged 65 years or older residing in Norway. Influenza vaccination coverage is the main outcome, measured in control and intervention arms for each of the 3 populations listed earlier. In all 3 populations, the control arm is standard care, that is, no individual reminder for influenza vaccination. All populations have an intervention arm that will receive an SMS nudge in the Norwegian language. In addition, the Polish and Ukrainian immigrant populations include a second intervention arm that will receive an SMS nudge in Polish or Ukrainian, respectively. In the general population, at least 23,485 individuals will be randomized to the SMS intervention arm while the rest of the population constitutes the control arm. In each of the 2 immigrant populations, we will randomize all eligible individuals 1:1:1 into the 3 arms. The intervention will take place at the start of the 2025-2026 influenza season. All eligible individuals will be passively followed up through the National Immunisation Registry, SYSVAK, from which individual influenza vaccination status 3 months after the SMS nudge will be collected. Coverage rates between arms within each population and effect sizes between the populations will be compared. The cost-effectiveness of SMS nudging will also be assessed.

**Results:**

The inclusion of participants will start in the third quarter of 2025, and the registry data will be available in the first quarter of 2026. Coverage rates of each strategy and coverage differences between strategies will be presented.

**Conclusions:**

SMS nudging is a scalable, inexpensive, and nonintrusive intervention that could be integrated into the national influenza vaccination program if the trial shows it effectively increases influenza vaccination coverage among older adults. Further, the trial will establish whether language is a barrier to influenza vaccination uptake among recent immigrant groups that have low influenza vaccination coverage, and to what extent this potential barrier can be diminished by SMS nudging in the official language of their native country.

**Trial Registration:**

ClinicalTrials.gov NCT06486766; https://clinicaltrials.gov/study/NCT06486766

**International Registered Report Identifier (IRRID):**

PRR1-10.2196/63938

## Introduction

### Background

Seasonal influenza has a high disease burden worldwide and may cause up to 5 million severe cases and 645,000 deaths annually [1]. Vaccination against influenza is generally safe and may be effective in reducing influenza-like illness and associated conditions [2-4]. It is a widely recommended public health intervention [5,6], especially for groups experiencing a disproportionately high influenza burden such as older adults, who have a higher risk of severe disease, hospitalization, and mortality [7,8]. However, influenza vaccination coverage generally falls far below the 75% target set by the World Health Organization [9], thus many older adults that could have benefitted from vaccination remain unprotected. Furthermore, vaccine hesitancy, defined as a “delay in acceptance or refusal of vaccination despite availability of vaccination services” [10], is widespread for influenza vaccination [11]. The World Health Organization has defined vaccine hesitancy as one of the 10 current threats to global health [12].

Several immigrant groups have shown a relatively low vaccination coverage in their adopted country and a relatively high burden of vaccine-preventable disease [13,14]. This may partly be related to differences in vaccine hesitancy, which may differ between countries [15,16]. It may also be associated with more limited access to vaccination among some immigrant groups, for instance, if immigrants do not understand the language in their adopted country. Whatever the reason, efforts are needed to narrow the gap in vaccination coverage and to promote public health as well as health equity. Tailored interventions addressing acceptability and access barriers faced by immigrants may be useful to achieve this end [14,17].

Vaccine hesitancy is a complex phenomenon that has several psychological components [18,19] that may be influenced by public health interventions that facilitate action and reduce barriers to uptake [20,21]. Behavioral nudges may improve compliance with the use of primary health care services [22], including influenza vaccination uptake among older adults [23]. However, the effectiveness of nudging varies substantially by mode, content, and population [24]. Nudging by reminding older adults to vaccinate against influenza has proven effective in increasing coverage but with far higher effectiveness for reminders sent by ordinary mail [25] than by a governmental electronic letter system [26]. SMS text message nudging may improve childhood vaccination [27], COVID-19 vaccination among health system employees [28], and influenza vaccination among patients due for a routine primary care visit [29]. However, a recent systematic review of randomized control trials (RCTs) on text messaging for improving vaccine uptake shows that very few trials have addressed influenza vaccination among older adults [30].

Norway’s influenza vaccination program recommends vaccination to people aged 65 years or older, as well as to other risk groups and health care personnel. Each municipality organizes local vaccination of risk groups. Vaccination is typically available at general practitioner’s offices, health clinics, and pharmacies, and is currently offered at an out-of-pocket cost ranging from NOK 150 to 500 (US $14 to $47). In general, vaccination at general practitioners requires the vaccinee to schedule an appointment, while vaccination at pharmacies can be drop-in or scheduled. There is no individual invitation, reminder, or scheduling for vaccination organized by the influenza vaccination program. COVID-19 vaccination is also recommended to the same age group at the same time of year. The same vaccination conditions apply to all residents of Norway, regardless of their citizenship or legal residency status.

InfluSMS is designed as a pragmatic, multiarmed, superiority RCT embedded in the Norwegian influenza vaccination program. In this trial, we aim to determine if sending a smartphone SMS nudge to be vaccinated against influenza can improve vaccination coverage in the general population aged 65 years or older in Norway, and further, to determine the impacts on vaccination coverage associated with providing an SMS nudge in the official language of the native countries of immigrants born in Poland or Ukraine. The Norwegian setting is well suited to conduct an RCT on SMS nudging among older adults, including in selected immigrant groups because there are nationwide administrative and health registries that can be used for this purpose.

An RCT on SMS nudging for influenza vaccination among older adults is warranted because the coverage is insufficient and because evidence on the effectiveness of this intervention is lacking [23,30]. Moreover, most older adults in Norway have a smartphone, thus an SMS intervention is likely to reach most of the eligible population. It is also a relatively nonintrusive and inexpensive intervention that is highly scalable, which thus could function as part of a national influenza vaccination program.

On average the influenza vaccination coverage among older individuals in Norway is 64%. However, the coverage among some immigrant groups is much lower. Immigrants born in Poland and Ukraine have especially low coverage rates with only 19% and 3% vaccinated in the 2023-2024 influenza season, respectively (Table 1). Poles and Ukrainians are the 2 largest immigrant groups in Norway. As of March 2024, there were 110,000 and 66,000 immigrants from Poland or Ukraine, respectively, accounting for 2.0% and 1.2%, of the entire Norwegian population. Even though the age profile of immigrants from Poland and Ukraine is younger than for some other country backgrounds, they still account for many older adult individuals (Table 1), and this demography is likely to increase in the coming years. Furthermore, Poles and Ukrainians are relatively recent immigrants and may as such have a limited proficiency in Norwegian. If this language barrier hinders their uptake of services, it could potentially be reduced by providing nudges in the official language of their native country.

**Table 1 table1:** Nationwide coverage^a^ of influenza and COVID-19 vaccine among individuals aged 65 years or older^b^ during the 2023-2024 influenza season in Norway, stratified by country background^c^.

	Total population	Influenza vaccine^d^ , n (%)	COVID-19 vaccine^e^, n (%)
All	1,020,728	656,990 (64.4)	555,745 (54.4)
Born in Norway	941,657	623,598 (66.2)	530,923 (56.4)
Born in Sweden	7129	4520 (63.4)	3976 (55.8)
Born in Denmark	5966	3820 (64.0)	3372 (56.5)
Born in United Kingdom	4606	2888 (62.7)	2594 (56.3)
Born in Germany	3991	2000 (50.1)	1783 (44.7)
Born in Poland	3888	740 (19.0)	520 (13.4)
Born in Ukraine	3843	119 (3.1)	72 (1.9)

^a^Norwegian Immunisation Registry SYSVAK [31] data, extracted May 31, 2024.

^b^Age on December 31, 2023 (born 1958 or earlier).

^c^The most common country backgrounds among individuals aged 65 years or older.

^d^Received at least 1 dose of influenza vaccine between September 1, 2023, and May 29, 2024.

^e^Received at least 1 dose of COVID-19 vaccine between September 1, 2023, and May 29, 2024.

Poles and Ukrainians in Norway also had a very low uptake of the COVID-19 vaccine, both during [32] and after (Table 1) the pandemic, showing that low uptake of adult vaccines in these populations is not limited to influenza vaccination. Thus, interventions that may overcome vaccine hesitancy, which is prominent in Ukraine and Poland [15,16], as well as potential access barriers such as language, are likely to have a general relevance for vaccine uptake.

A recent systematic review highlighted language and tailored text message nudges for improving vaccine uptake as understudied [30]. We are not aware of any studies that have investigated the effectiveness of SMS nudging for influenza vaccination in several languages among immigrant populations.

### Objectives

The primary objectives of the InfluSMS trial are to establish whether (1) influenza vaccination nudging by SMS in the Norwegian language increases influenza vaccine coverage compared to standard care, among the Norwegian population aged 65 years and older; (2) influenza vaccination nudging by SMS in Polish or Ukrainian language increases influenza vaccine coverage compared to standard care, among older adults of Polish or Ukrainian background, respectively; (3) influenza vaccination nudging by SMS in Norwegian language increases influenza vaccine coverage compared to standard care, among older adults of Polish or Ukrainian background, respectively; and (4) influenza vaccination nudging by SMS in Polish or Ukrainian language increases influenza vaccine coverage more than nudging by SMS in Norwegian language among older adults of Polish or Ukrainian background, respectively.

For primary objectives 1-3, we hypothesize that SMS nudging will increase coverage. If this hypothesis is not confirmed, the interventions investigated here are futile from a public health perspective, and the remaining study objectives will not be investigated. For primary objective 4, we hypothesize that an SMS in the official language of the native country of each immigrant population will be more effective in increasing coverage than an SMS in Norwegian.

The secondary objectives are to establish whether (1) the effect of SMS nudging in the Norwegian language differs by country background; (2) the effect of SMS nudging in the official language of their native country differs between older adults of Polish or Ukrainian background; (3) SMS nudging for influenza vaccination is cost-effective compared to standard care; (4) SMS nudging for influenza vaccination influences coverage of COVID-19 vaccination; and (5) the time to vaccination differs by the comparisons described in the primary objectives.

Secondary objectives 1-4 are exploratory and have no hypotheses. For secondary objective 5, we hypothesize that SMS nudging will shorten the time elapsed to vaccination.

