### Sample Size

#### Primary Objective 1: General Population in Norway

We will identify all individuals in the National Population Register that fulfill the eligibility criteria, and among those, make a random selection to receive the Norwegian nudge (intervention 1). We power for a 1% point minimal detectable increase in uptake in the SMS arm compared to the control arm in the general population because the intervention is relatively inexpensive and might be cost-effective even with low effectiveness on coverage. To achieve this minimal detectable increase with a baseline uptake rate of 60%, a power of 0.8, and a 1-sided α of .05, we need to randomize 18,788 individuals to intervention 1. However, based on available statistics, some 20% of individuals may have received the influenza vaccine before the scheduled trial start date and will be excluded from the trial after randomization. We thus need to randomly sample at least 23,485 individuals aged 65 years or older from the entire Norwegian population (except those born in Poland or Ukraine) to be allocated to intervention 1 to be able to detect an increase of 1 percentage point (23,485×80/100=18,788). The control group will be the rest of the Norwegian population that fulfills the eligibility criteria. Currently, there are circa 1.1 million persons aged 65 years or older who reside in Norway. We use this large group as a control because it gives the study high power, the inclusion of individuals receiving standard care carries no cost, and it will provide real-world data on the entire older adult population in Norway.

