#### Primary Objectives 2-4: Immigrants Born in Poland or Ukraine

To maximize power among individuals born in Poland or Ukraine, we will include all eligible individuals and randomly assign them 1:1:1 to each of the 3 study arms. The number we will be able to include in the trial will most likely be higher in 2025 than in 2023 (Table 1) due to the age structure in these immigrant populations and due to new migration. Based on current national demographic statistics, we anticipate there will be some 6000 individuals aged 65 years or older from each immigrant group at the start of the trial. However, some 10% may be excluded due to not having a registered phone number, and a further 1% and 6% (Table 1) may be excluded due to influenza vaccination before the scheduled SMS dispatch date among the Ukrainian and Polish immigrant populations, respectively. Thus, we expect to be able to randomize 5346 Ukrainian immigrants, giving 1782 individuals in each study arm. With a baseline uptake rate of 3% (Table 1), a power of 0.8, and a 1-sided α of .05, this gives a minimal detectable coverage increase of 2 percentage points, adjusted for 3 pairwise comparisons. Similarly, we expect to be able to randomize 5076 Polish immigrants, giving 1692 individuals in each study arm. With a baseline uptake rate of 19% (Table 1), a power of 0.8, and a 1-sided α of .05, this gives a minimal detectable coverage increase of 4% points, adjusted for 3 pairwise comparisons.

In conclusion, the minimal detectable coverage increases of this trial fall within the range of effect sizes reported for other modes of nudging investigated in neighboring countries that share a similar influenza vaccination policy. Specifically, a recent study from Denmark reported that nudging by electronic letters increased coverage by approximately 1% points [26], while a recent study from Finland reported that nudging by ordinary mail on average increased coverage by approximately 6% points [25].

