The trial also has several limitations, most of which relate to the number of Polish and Ukrainian immigrants we will be able to randomize. First, the number of persons in the immigrant groups who are aged 65 years or older in the 2025-2026 influenza season is a moving target that will be influenced by the influx and outflux of people by that time, as well as the exact underlying age distribution of these immigrant populations. Second, our estimates of the fraction of people missing a registered smartphone number are based on statistics for the whole Norwegian population, and we do not know whether this fraction may be different for the Polish and Ukrainian sub-populations. Third, the minimum detectable effect size for the Polish and Ukrainian populations is approximately 4% and 2% points, respectively. This may be a limitation because even smaller effect sizes might be of public health interest for an inexpensive intervention. Finally, even though we will initiate the trial at the very start of the influenza season, some people will already have been vaccinated by this point, and they will be excluded from participation in the trial. The number of excluded individuals will depend on national vaccine distribution logistics and the epidemiology of influenza in the trial season, which are beyond our control.

The current influenza vaccination program lacks an individual cue to action, which could potentially be more effective than a general recommendation that lacks personalization or direct communication. Sending SMS nudges for influenza vaccination is one way to make individual contact that is likely to reach a very large proportion of the eligible population. If sending SMS reminders is effective, even small effect sizes may benefit public health and be cost-effective. Furthermore, nudges tailored to immigrant groups that have very low uptake of influenza vaccine may reduce inequalities in the use of this preventive health care service and, thus, in health. Insights from the interventions investigated in the current trial can extend to other vaccination contexts and be of international relevance.

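### An unconfirmed superiority hypothesis is read as public health futility, with no margin or confidence bound, although the Discussion says effects below the detectable size might matter

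*Protocol article*

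**What the plan says.** The trial is a superiority design (Introduction, Background: "InfluSMS is designed as a pragmatic, multiarmed, superiority RCT embedded in the Norwegian influenza vaccination program"). In the Objectives section the hypothesis is directional: "For primary objectives 1-3, we hypothesize that SMS nudging will increase coverage". The consequence of failure follows at once: "If this hypothesis is not confirmed, the interventions investigated here are futile from a public health perspective". The same sentence cancels the remaining objectives. That cancellation is a separate matter and is not part of this point.

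The Sample Size section plans for 1 percentage point in the general population. For the Polish group it says "this gives a minimal detectable coverage increase of 4% points, adjusted for 3 pairwise comparisons", and it gives the corresponding figure for the Ukrainian group as 2 points. The Discussion lists these two detectable effects among the limitations and comments: "This may be a limitation because even smaller effect sizes might be of public health interest for an inexpensive intervention".

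Statistical Methods and Results plan absolute and relative differences with 95% confidence intervals, with the main focus on the absolute scale. Neither section links the intervals to the futility conclusion.

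**The concern.** A superiority hypothesis can go unconfirmed for two reasons: there is no useful effect, or the data are too imprecise to show one. The Objectives sentence treats both as futility. To conclude that a worthwhile effect is absent, one has to show that the data exclude such an effect, and the sentence asks for no such showing.

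The Discussion concedes that the immigrant comparisons cannot reliably detect effects that might matter. An unqualified statement that the interventions are futile when detection fails cannot stand beside that concession. At stake is a published conclusion that a cheap, scalable intervention is futile, drawn from inconclusive data in the two groups with the lowest coverage (19% and 3% in Table 1).

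**Working it through.** **Inputs (Sample Size section).** Polish group: 1692 per arm, baseline 19%. Ukrainian group: 1782 per arm, baseline 3%. One-sided alpha .05, power 0.8, adjusted for 3 pairwise comparisons. The adjustment method is not named, so I assume .05/3 = .0167. General population: 18,788 nudged, baseline 60%; I assume about 700,000 controls, a number that hardly affects the standard error.

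**Formula.** Power = Φ[(d − z·S0)/S1], where d is the true difference, S0 = √(2p̄(1−p̄)/n) and S1 = √(p0(1−p0)/n + p1(1−p1)/n).

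**Reproducing the plan's figures, alpha .0167 (z = 2.128).**
- Polish, d = 4 points: S0 = √(2×0.21×0.79/1692) = 1.400 points and S1 = 1.399. (4 − 2.128×1.400)/1.399 = 0.73, so power is 0.767. Power 0.8 is reached at 4.16 points.
- Ukrainian, d = 2 points: S0 = √(2×0.04×0.96/1782) = 0.656 points and S1 = 0.656. (2 − 2.128×0.656)/0.656 = 0.92, so power is 0.821. Power 0.8 is reached at 1.94 points.

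Both round to the stated 4 and 2 points, which the Discussion calls approximate.

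**Chance that a real benefit goes unconfirmed, one comparison.** At Polish +2 points, S0 = S1 = 1.375. With alpha .05, (2 − 1.645×1.375)/1.375 = −0.19, so power is 0.42 and failure 58%. With .0167, (2 − 2.128×1.375)/1.375 = −0.67, so power is 0.25 and failure 75%. Simulation with 400,000 replicates (unpooled Wald test) agrees and gives the other cells:

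| True effect | one-sided .05 | .025 (as in a 95% CI) | .0167 |
|---|---|---|---|
| Polish +2 points | 58% | 69% | 75% |
| Polish +3 points | 30% | 42% | 49% |
| Ukrainian +1 point | 51% | 63% | 69% |
| Ukrainian +1.5 points | 24% | 34% | 41% |
| General +0.5 point | 60% | 72% | – |
| General +1 point | 13% | 21% | – |

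Power crosses 50% at 2.27 points (.05) or 2.95 points (.0167) in the Polish group, and at 1.01 or 1.34 points in the Ukrainian group. Below those values failure is the likelier result.

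**What a non-significant result leaves open.** With an observed difference of exactly zero, the 95% half-width is 1.96×√(2×0.19×0.81/1692) = 2.64 points (Polish) and 1.96×√(2×0.03×0.97/1782) = 1.12 points (Ukrainian). A 1-point benefit is excluded in neither group. Among trials whose 95% CI includes zero, the upper limit still reaches the plan's design effect in 56% (Polish, true +2), 41% (Ukrainian, true +1) and 61% (general, true +0.5).

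**Scope.** Suppose futility requires all five nudge-versus-control comparisons to fail, with Polish +2 and Ukrainian +1 points. Both Polish nudge arms fail in 41% of trials at .05 and 62% at .0167; both Ukrainian arms fail in 34% and 55%.
- General +1 point: 0.13×0.41×0.34 ≈ 2%, up to 0.21×0.62×0.55 ≈ 7%.
- General +0.5 point: 0.60×0.41×0.34 ≈ 8%, up to 0.72×0.62×0.55 ≈ 25%.

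If instead every comparison must succeed, the four immigrant comparisons alone all succeed in only 8.5% (.05) or 2.0% (.0167) of trials at these effects, so the label would follow in at least 91% or 98%.

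**The case against.** The strongest reply is about scope. The Objectives section speaks of a single hypothesis over objectives 1-3 and of the interventions together. A fair reading is that the programme is futile only if nudging is not shown to work anywhere, and the label would then be uncommon. This stands. The per-comparison rates hold only on the per-comparison reading. It does not rescue the inference: failure of all comparisons is still non-significance, and no upper limit has been examined.

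A reader might infer that the label would usually be applied to any effect below the detectable size. The figures do not support that. At Polish +3 and Ukrainian +1.5 points failure is the minority outcome at every alpha examined.

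A reader might also count two further sentences as contradictions. The first, "If sending SMS reminders is effective, even small effect sizes may benefit public health and be cost-effective", is conditional on effectiveness and does not address an unconfirmed hypothesis. The second, "the intervention is relatively inexpensive and might be cost-effective even with low effectiveness on coverage", explains why the general population is powered for 1 point; there, failure at a true +1 point is 13-21%, which is ordinary type II error. Neither contradicts the rule. The conflict rests on the one sentence in the Discussion limitations, and that sentence is hedged. Even so, an effect that might be of interest cannot also be covered by an unqualified statement of futility.

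Finally, confidence intervals will be published, so readers can see the upper limits. True, but the stated conclusion does not depend on them. Nor is this a detail left to an analysis plan: it is a rule the protocol states.

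**Conclusion.** The point holds in this form: the protocol infers public health futility from an unconfirmed superiority hypothesis, without a margin or bound, and this conflicts with its own Discussion. The scope of the rule is unclear.

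The size depends on that scope. Per comparison, a real benefit is labelled futile more often than not for Polish effects below about 2.3-3.0 points and Ukrainian effects below about 1.0-1.3 points, but not for larger ones. If all comparisons must fail, the label is much rarer. On no reading does non-significance establish futility.

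The figures assume the planned numbers per arm, the stated baselines, an alpha between one-sided .05 and .05/3, and the assumed general-population control size. The protocol names no smallest worthwhile effect for the immigrant groups, so the effects in the table are illustrations.

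**What to change.** Rewrite the Objectives sentence as follows.

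1. Delete the futility wording as the reading of an unconfirmed hypothesis.
2. State that the conclusion is drawn separately for each population and comparison.
3. Declare effectiveness by the plan's own test and alpha, including the adjustment for 3 comparisons in the immigrant groups. Do not substitute a 95% lower limit above zero. That is an unadjusted one-sided .025: stricter than planned in the general population (failure at +1 point rises from 13% to 21%) and looser than .0167 in the immigrant groups.
4. When the test is not met, read the planned 95% CI for the absolute difference. If its upper limit is below the design effect (1 point general, 4 Polish, 2 Ukrainian), report only that an effect of that size is excluded. In the immigrant groups, add that smaller effects of possible interest are not ruled out. Otherwise report the result as inconclusive.

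With no true effect, the upper limit falls below the design effect in about 79% (general), 84% (Polish) and 94% (Ukrainian) of trials. In the immigrant groups this excludes 4 or 2 points and nothing smaller.

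The cost is one paragraph, with no new data or participants. The downside is that some negative results will be called inconclusive.

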## Results

As of July 3, 2024, the project has received funding for protocol development from Foundation Dam (grant SDAM_FOR-558766) and we are in the process of obtaining permits, agreements, and access to the infrastructure needed to conduct the trial. Inclusion of participants will start in the third quarter of 2025 and the outcome registry data will be available in the first quarter of 2026. We plan to publish the results during the fourth quarter of 2026.

The results will be reported according to the Consolidated Standards of Reporting Trials (CONSORT) statement on eHealth [45,46]. We will present the baseline characteristics of the 3 study populations, and describe the coverage by treatment arm and population, for strata of age, sex, and duration of residency. We will present the absolute and relative coverage differences between the treatment arms as described in objectives 1-4. In addition, we present comparisons of effect sizes between populations as described in secondary objectives 1 and 2, on absolute and relative scales. The primary focus will be on absolute scale analyses for the coverage analyses (primary outcome measure). We also compare the time to vaccination between treatment arms (the secondary outcome measure). All effects are presented with 95% CIs. We also present the likelihood ratio test *P* value for interaction terms. Table shells for the analyses described earlier can be found in Multimedia Appendix 1. The main findings may also be illustrated in the figures.

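### An undefined condition on objectives 1–3 can cancel the native-versus-Norwegian language comparison, and it contradicts unconditional promises elsewhere in the protocol

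*Protocol article*

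**What the plan says.** The Objectives section lists four primary objectives. The first three compare an SMS with standard care: Norwegian SMS in the general population, native-language SMS in each immigrant group, and "3) influenza vaccination nudging by SMS in Norwegian language increases influenza vaccine coverage compared to standard care, among older adults of Polish or Ukrainian background". For these it states one hypothesis: "For primary objectives 1-3, we hypothesize that SMS nudging will increase coverage". The next sentence attaches a consequence to failure: "the interventions investigated here are futile from a public health perspective, and the remaining study objectives will not be investigated". What remains is primary objective 4, whose own hypothesis is that the native-language SMS raises coverage more than the Norwegian one, and all five secondary objectives (two comparisons of effects between populations, cost-effectiveness, COVID-19 vaccination and time to vaccination).

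Three other places bear on this:
- Abstract, Conclusions: "the trial will establish whether language is a barrier to influenza vaccination uptake among recent immigrant groups".
- Results: "We will present the absolute and relative coverage differences between the treatment arms as described in objectives 1-4".
- Discussion, on detectable effects in the immigrant groups: "This may be a limitation because even smaller effect sizes might be of public health interest for an inexpensive intervention".

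None of the three mentions a condition.

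**The concern.** The rule treats five comparisons as one hypothesis and leaves open whether all, some or one must succeed. The choice matters because objective 3 is inside the condition. The Introduction justifies the native-language arm by the possibility that recent immigrants read Norwegian poorly. If that is true, the Norwegian SMS is the intervention most likely to fail in these groups, and its failure could forbid the very comparison that would show why.

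At stake is a primary objective and the trial's distinctive question. Because the reading is not fixed, it could also be chosen after the results of objectives 1–3 are known.

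The rule further equates an unconfirmed hypothesis with futility, although the Discussion accepts that effects too small to be detected may matter.

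**Working it through.** **1. Comparisons inside the condition.** General population 1, plus 2 languages × 2 immigrant groups = 5.

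**2. Inputs (Sample Size section).**
- Poland: 1692 per arm, baseline 19%, detectable increase 4 points.
- Ukraine: 1782 per arm, baseline 3%, detectable increase 2 points.
- Both: 1-sided α of 0.05 adjusted for three comparisons, taken here as 0.05/3 (critical value 2.128).
- General population: 18,788 in the SMS arm, baseline 60%, increase 1 point, 1-sided 0.05 (critical value 1.645).
- Assumption: 850,000 controls remain after exclusions. A range of 500,000 to 1,000,000 moves that test's power only from 0.866 to 0.871.

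**3. Reproducing the plan's figures.** Power = Φ[(δ − z·s₀)/s₁], where s₀ is the pooled and s₁ the unpooled standard error of the difference.
- Poland: s₀ = √(2 × 0.21 × 0.79/1692) = 0.01400 and s₁ = 0.01399. (0.04 − 2.128 × 0.01400)/0.01399 = 0.729, so power is 0.767.
- Ukraine: s₀ = √(2 × 0.04 × 0.96/1782) = 0.00656 and s₁ = 0.00656. The same formula gives 0.920, so power is 0.821 (0.83 by simulation).
- General population: s₀ = 0.00361 and s₁ = 0.00360. (0.01 − 1.645 × 0.00361)/0.00360 gives about 1.13, so power is 0.870.

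Solving for 80% power gives 4.16 points (Poland) and 1.94 points (Ukraine), which round to the stated 4 and 2. The adjusted 1-sided reading is therefore the plan's own.

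**4. Probability that the condition is met.** Simulation with pooled z tests, a shared control arm within each immigrant group and independent populations. The native-language SMS has the planned effect throughout.

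| Reading of the condition | Norwegian SMS at planned effect | Half effect | No effect (total barrier) |
|---|---|---|---|
| All five succeed | 0.40 | 0.06 | 0.0002 |
| Both SMS comparisons within one population (Poland / Ukraine) | 0.64 / 0.72 | 0.24 / 0.29 | 0.016 / 0.016 |
| Each objective in at least one group | 0.81 | 0.41 | 0.03 |
| Any one succeeds | 0.999 | 0.996 | 0.995 |

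Hand checks for the last column:
- All five: 0.870 × 0.0165 × 0.0162 = 0.00023.
- Each objective: the chance that a null Norwegian SMS succeeds in at least one group is 1 − (1 − 0.0167)² = 0.033, and 0.033 × 0.870 = 0.029.

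**5. Power of objective 4 itself.** Under a total barrier the Norwegian arm behaves like the control arm, so the power is that of step 3: about 0.77 and 0.83. With a half-size Norwegian effect it is much lower:
- Poland (21% v 23%): 0.02/√(2 × 0.22 × 0.78/1692) = 1.404, and Φ(1.404 − 2.128) = 0.23.
- Ukraine (4% v 5%): 0.01/√(2 × 0.045 × 0.955/1782) = 1.440, and Φ(1.440 − 2.128) = 0.25.

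The conflict is therefore sharpest when the barrier is complete.

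**6. Sensitivity of the all-five figure at planned effects (0.40).**
- General test at 1-sided 0.025: 0.37.
- All tests at 1-sided 0.025: 0.44.
- All tests at unadjusted 1-sided 0.05: 0.62.
- Native-language SMS exceeding the Norwegian SMS by the detectable difference (8 v 4 and 4 v 2 points): 0.55.

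**The case against.** **The requirement that all five succeed is only one reading.** The hypothesis is in the singular, and the text calls the interventions as a whole futile, which fits best if none of them works. On that reading the condition is met in over 99% of trials and the language question is answered. This stands. A reader might infer that the rule cancels objective 4 exactly when a language barrier exists, or that it usually blocks the remaining objectives even at the planned effects. The text supports neither. The first fails when one success is enough. The second holds only if all five must succeed at an α stricter than unadjusted 1-sided 0.05, and not if the native-language SMS beats the Norwegian one by the detectable difference.

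**Error control for objective 4 does not depend on the rule.** The Sample Size section already adjusts for three pairwise comparisons in each immigrant population. This also stands. The lenient reading therefore does no inferential harm, and a new testing sequence is not needed.

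**The Results section is an outline and need not repeat a condition; details belong in an analysis plan.** This stands in part. The number of successes required could be defined in an analysis plan. But the protocol itself states the rule, and the rule can remove a primary comparison that the Abstract says the trial will deliver. The Results section also plans to describe coverage by arm, so arm-level figures would probably be visible, but not the planned comparison.

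**Nothing is lost irreversibly.** True: follow-up is passive, and there are no interim analyses or stopping guidelines. For the same reason the rule spares participants nothing and only withholds analyses.

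**Conclusion.** The point holds in limited form. The protocol makes objective 4 and every secondary objective depend on an undefined condition that includes objective 3. On three of the four readings examined, a total language barrier would almost always cancel the native-versus-Norwegian comparison (condition met with probability of about 0.0002, 0.016 or 0.03), although that comparison would have power of about 0.77 and 0.83. On the fourth reading the rule has practically no effect. At the planned effects the condition is met with probability of about 0.40 if all five must succeed at the adjusted α, and 0.64 to 0.999 otherwise. It would therefore be wrong to say that the trial is generally likely to lose these objectives.

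These figures assume the protocol's sample sizes and baselines, an adjustment of 0.05/3, and about 850,000 controls. The contradictions with the Abstract, Results and Discussion need no assumption.

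**What to change.** Delete the sentence in Objectives that declares the interventions futile and drops the remaining objectives. Replace it with wording such as: *Estimates and confidence intervals for primary objectives 1–4 and all secondary objectives will be reported whatever the result of objectives 1–3. In each immigrant population, objective 4 will be tested under the adjustment for three pairwise comparisons used in the sample size calculation.*

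Testing objective 4 in a population only if objective 2 is confirmed there is an acceptable alternative, but it is optional. If the sponsor prefers to keep a condition, the protocol should state which comparisons must succeed, in which population and at what α, should leave objective 3 out of the condition for objective 4, and should bring the Abstract and Results into line.

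The cost is protocol wording and a registry note, with the amendment notices that the protocol already provides for, made before outcome data are available. No extra data or participants are needed.
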